### Place and staffing requirements

2.4

The screening site will be community pharmacies with suitable cognitive screening space. A suitable space may be a separate room in the pharmacy or a separate part of another area to guarantee confidentiality for the patient. Only trained pharmacists or pharmacy students under the supervision of a trained pharmacist may perform the screening. The pharmacist enrolled in the study must also provide the name and address of the pharmacy where the screening will be conducted.

Participating pharmacists will be educated through a 2-h webinar followed by a workshop with a pharmacists´ competency assessment, according to Rickles and colleagues (8), which will be prepared and implemented with the cooperation of the Slovak Chamber of Pharmacists, the Faculty of Pharmacy of Comenius University Bratislava, the University of Veterinary Medicine and Pharmacy in Kosice and medical societies. Trained pharmacists will be trained in using cognitive screening tools and the MoCA Test, receive information on modifiable risk factors for dementia and early warning signs, and gain practical experience in strategies to identify at-risk patients within pharmaceutical care. The training program will also provide a detailed overview of study consent forms and documents, an overview of the patient care process, dementia risk assessment, and an overview of protocols for patient follow-up, data collection, and reporting.

### Personal competence

2.5

Collecting data and performing cognitive screening – trained pharmacists or pharmacy students under the supervision of a trained pharmacist.Interpretation of results – trained pharmacists only.Patient outcomes should be communicated to the physician–pharmacists only.

#### The target group of individuals for which the screening is recommended

2.5.1

Aged 50+.Suffering from cardiovascular disease and/or 2 type diabetes mellitus (in case of DM2 without age limitation).With dementia risk factors according to the CAIDE score.With a family history of cognitive disorders (MCI, dementia, Alzheimer’s disease).With at least one of the Alzheimer’s disease international early warning signs.

### Cognitive screening

2.6

The gold standard screening tool, the Montreal Cognitive Assessment (MoCA), one of the available cognitive screening instruments, scans seven cognitive domains: executive functioning; visuospatial abilities; language; attention, concentration and working memory; abstract reasoning; memory and orientation, will be used. We use the short variant (s-MoCA) (28, 29) in the Slovak language, presenting a comparable alternative for detecting MCI and dementia. This short variant consists of 8 items. These items measure visuospatial and executive functions (trail making and clock drawing), language abilities (animal naming – rhinoceros), attention (serial 7 s – counting by subtracting seven), verbal fluency (naming for 1 min), abstraction (watch), delayed recall of words, orientation (place) (29). According to our previous outcomes, this simple, shortened version is an easy-to-use cognitive screening. It is an applicable compound of pharmaceutical care for adult patients aged 50 and older with cardiovascular disease and/or suspected metabolic syndrome (sMetS) to explore their cognitive state. This shortened form of the MoCA scale has a range of 0–16 points; the time of completion is 5–7 min (which is only one-third the length of the original MoCA), and a cut-off of ≤12 represents a cognitive impairment (29).

### Assessment of dementia risk factors

2.7

The CAIDE scoring system will be applied to the occurrence of modifiable risk factors (31). It was designed to determine the risk of developing dementia in cognitively intact individuals aged 40 to 65 years. This tool assesses common, easy-to-obtain, measurable data such as age, sex, education, blood pressure, cholesterol level, BMI, and physical activity. Each item is scored, and the resulting score represents the level of risk of developing cognitive impairment or dementia. The cut-off score represents 8–9 points for low and normal risk. Higher scores (10–15) indicate an increased risk of developing cognitive impairment (31).

We will also assess an occurrence of the suspected MetS (sMetS) as it can be easily identified in community pharmacy and may affect cognitive function (40, 44). The presence of sMetS will be estimated according to the International Diabetes Federation Worldwide Definition of MetS (45), 2005, modified for the European population (46). Accordingly, patients will be divided into groups according to the presence or absence of sMetS (sMetS+; sMetS-), and we will compare cognitive abilities in the test s-MoCA between two subpopulations (sMetS+/sMetS-) (40).

### Analysis of chronic medication

2.8

Medication analysis will be focused on the identification of at-risk medication use with an anticholinergic burden risk used in included participants. We will assess the cumulative effect of medication with anticholinergic properties taking long-term, which can adversely impact cognitive performance and physical abilities and increase the mortality risk (15). We will use an expert opinion-derived risk scale, the ACB Scale, which helps quantify the risk of anticholinergic burden (17). The list of at-risk medications is summarized in Supplementary Table 1. The scale ranks the anticholinergic activity of drugs into four categories, according to their anticholinergic effect and potential for impairment of cognition: (i) no anticholinergic activity, ACB = 0; (ii) possible anticholinergic activity, ACB = 1; (iii) definite anticholinergic activity, ACB = 2; and (iv) definite high anticholinergic activity, ACB = 3 (15). Medication with the scores 1, 2 and 3 can be found in Supplementary Table 1. If the medication is not displayed in the list, its ACB score equals 0. In patients taking more than one medication from the list, scores are cumulative, and a total score ≥3 means a high risk for cognitive impairment. Each one-point increase in the ACB total score is associated with an apparent decline in the MMSE score (16).

### Patient counseling

2.9

Pharmaceutical counseling will be provided to patients concerning their needs, family and personal history and comorbidities or even physician’s recommendation (Supplementary Table 2). The analysis plan is shown in Figure 3. During the interpretation of the results of cognitive screening (following initial screening or, if necessary, after retesting 6 months later, by the patient’s consent and an agreed appointment with the pharmacist based on a call), it is essential to explain to the patients that this simple cognitive screening is not a substitute for a medical examination and that the result of the screening is not a physician’s diagnosis. Next, the pharmacist will provide a patient’s education about other factors that may influence cognitive decline (such as stress, lifestyle, sleep disturbances, depression and certain medications or substance use, e.g., caffeine, alcohol). Patients will get printed educational materials about risk factors for cognitive impairment and early warning signs of dementia.

**Figure 3 fig3:**
[figure not shown]
Analysis plan – counseling between pharmacist and patient.

According to results of screening and pharmacist’s consideration, patients may be referred to a physician if their condition requires it. In such cases, the pharmacist will use the uniform information form for the physician (Supplementary Table 3). The patient receives an examination report informing the physician of the findings.

### Physician referral

2.10

For each patient, the pharmacist will specifically consider whether their condition requires a visit to the doctor or a pharmacy consultation is sufficient. The analysis plan is shown in Figure 4. Specific groups of patients are referred to a physician if they score decreased cognitive abilities on the s-MoCA test. Patients:

with memory problems,with at least one of the early signals of dementia,at risk of developing dementia, according to CAIDE,that do not have regular preventive check-ups,that are long-term users of at-risk medication (Supplementary Table 1),with long-term use of over-the-counter memory aids.

**Figure 4 fig4:**
[figure not shown]
Analysis plan – counseling between pharmacist and physician.

The result of the pharmacotherapy analysis will be received only by a doctor. The patient will not be given the results to maintain adherence. Every patient in the study should be referred to a general practitioner for a preventive check-up if they have not had one in the last 2 years. During follow-up, the pharmacist will contact patients electronically to obtain feedback on whether they have addressed their condition with a doctor and whether the presence of CI has been confirmed.

## Outcomes

3

In this study, we focus on a cohort of adults aged 50+ with lower cognitive abilities expressed by s-MoCA scores (≤ 12 points). These patients will be defined as those with suspected CI (CI+) who will be referred for medical examination. We will then record whether a physician has confirmed our suspicion of CI.

In the CI+ group, we will collect data on the prevalence of CI risk factors (expressed by CAIDE score) and the use of risk medications (expressed by ACB score) and then compare them with a control group.

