### Epidemiology and cognitive screening

1.1

Cognitive disorders represent a growing public health concern given the increasing number of seniors reaching an at-risk age (1, 2), associated with a subjectively or objectively measurable decline in at least one of the domains of cognitive functions, such as verbal abilities, spatial orientation, episodic memory, processing speed and executive functions (3). Only limited attention has been given to cognitive assessment in the community pharmacy targeting the early identification of undiagnosed cognitive impairment (CI) (4–9). As pharmacists are the most accessible health professionals due to the availability of community pharmacies to the public, they have the potential to be involved in early identification of at-risk patients who have not yet received a professional examination by a physician (4). Dementia and Alzheimer’s disease are the most common cognitive disorders affecting older people aged 60+ (1, 10), with a globally devastating impact on society with a disproportionate burden on health, economic and social care (11–13). Therefore, prevention, diagnosis, and pharmacological and non-pharmacological treatment of dementia are among the international priorities of the World Health Organization (WHO) (1, 2). It is essential to recognize CI at a reversible stage, and early intervention and appropriate interventions can prevent the development of dementia. This stage called mild cognitive impairment (MCI), is a transitional phase between cognitive ability decline due to age and the terminal stage of CI, dementia. Mental health and memory problems are crucial issues with significant impact on life quality. They can also affect patients’ level of medication adherence and self-care ability, which can result in poor long-term health outcomes (5, 8). Secondarily, cognitive decline may also be accelerated by the use of at-risk medications, especially when taking them for a long time (14, 15). These drugs suppress the cholinergic neurotransmitter pathways affecting brain structures such as the hippocampus and the neocortex, which are already vulnerable to age-related CI (16). Analysis of chronic pharmacotherapy can help identify at-risk medications and suggest a safe alternative, if possible. Anticholinergics, sedatives and benzodiazepines are the commonly used drugs with adverse effects on cognitive function (15–18). When they are combined, their adverse effect is cumulative (15, 19). A well-used tool is an assessment of the anticholinergic burden (ACB) scale (17). Implementing cognitive screening for early identification of patients with CI into pharmaceutical care can forward these patients to a doctor without undue delay and allow early initiation of their treatment and monitoring of further cognitive deterioration. Moreover, treatment of CI could reduce the risk of non-adherence to pharmacotherapy for already diagnosed chronic diseases (5, 20). Community pharmacists are suitable for preventing dementia by implementing cognitive screening within advanced pharmaceutical care (5, 20). Early identification of at-risk patients with CI could improve the availability of physician-indicated targeted treatment.

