### Cohort and sample size calculation

2.2

Adult patients aged 50 years or older receiving pharmaceutical care (patients who visit community pharmacy for different reasons, e.g., to collect a medication with/without prescription, pharmaceutical counseling, etc.) in community pharmacies in Slovakia who can complete the questionnaires and are willing to participate in the study will be included. Inclusion and exclusion criteria are shown in Table 1. Exclusion criteria also include disorders which can be related to cognitive dysfunction (e.g., schizophrenia). Pharmacy clients will receive written information about the study objectives, and consent will be obtained to confirm participation. By their signature, they will also agree to participate only once (to avoid duplicities). Individuals will be informed that participation is voluntary and can be terminated at any time. Also, they will be ensured that access to the collected data will be restricted to the study investigators only. The minimum sample size for our analysis was based on the estimated proportion. The sample size was set using an online sample size calculator for a 95% confidence interval and a 5% margin of error (42), according to previously used in Kosirova et al. (33). The minimum number of included subjects was estimated to be 385 according to the total number of adults aged 50 and over in 2023 (*N* = 2,033,555); (43).

**Table 1 tab1:** Inclusion and exclusion criteria.

Inclusion criteria	Exclusion criteria
Adults aged 50 and older, patients with type 2 diabetes mellitus without age limitation Undergoing at least one counseling by a pharmacist No previous diagnosis of CI/dementia as determined by ICD-10 codes or the presence of a prescription for anti-dementia medications (cholinesterase inhibitors or memantine) Ability to consent to participate in the study Ability to communicate in Slovak	Adults outside the age criteria Adults in permanent senior care or nursing home A serious mental illness such as schizophrenia code ICD-10 and targeting medication A pre-existing diagnosis of CI/dementia

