### Data collection

2.3

Data will be collected by trained pharmacists working in community pharmacies. They will be recorded on a pre-printed study form (socio-demographic data, lifestyle habits, evidence of comorbidities, and family history of Alzheimer’s disease and dementia). Table 2 summarizes all items that will be recorded.

**Table 2 tab2:** Basic characteristics and risk factors of the study population.

Socio-demographic features and lifestyle habits	
Age	Number of years
Gender	Multiple choice (*Female/Male*)
Education level	Number of school years
Waist circumference	Number (*cm*)
Physical activity habits	Open-ended questions (*frequency, duration per week, type of physical activity*)
Marital status	Multiple choice (*single/married/widow/divorced*)
Live in the household	Multiple choice (*alone/with other family members*)
Sleep duration	Open-ended questions (*frequency and duration per night/day*)
Smoking habits	Number of cigarettes per day
Alcohol consumption	Number and type of drinks per day
Comorbidities	
Hypertension	Yes/No
Dyslipidaemia	Yes/No
Type 2 diabetes	Yes/No
Overcome diseases	
Stroke	Yes/No
Thrombosis	Yes/No
Head injury	Yes/No
Actual and/or past problems	
Memory problems	Yes/No
Vision problems	Yes/No
Hearing problems	Yes/No
Smell problems	Yes/No
Family history of Alzheimer’s disease and/or dementia pathology (in line of parents, grandparents)	Yes/No

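### CI+ rests on one raw s-MoCA cut-off that is not checked against age or schooling, so the CI+ and confirmed shares may partly reflect participant mix, and the CAIDE contrast may be partly built in

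*Protocol article*

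**What the plan says.** Section 2.6 (Cognitive screening) gives the scale and the threshold: "This shortened form of the MoCA scale has a range of 0–16 points" and "a cut-off of ≤12 represents a cognitive impairment (29". Section 3 (Outcomes) uses the same threshold to form the study group, people with "lower cognitive abilities expressed by s-MoCA scores (≤ 12 points". The consequence follows at once: "These patients will be defined as those with suspected CI (CI+) who will be referred for medical examination". The next step is "We will then record whether a physician has confirmed our suspicion of CI". The CI+ group is then compared with a control group on CAIDE and ACB scores. Neither section mentions an age band, an education correction or a norm.

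The rule covers a wide population. Table 1 admits "Adults aged 50 and older, patients with type 2 diabetes mellitus without age limitation". Table 2 records age in years and education as "Number of school years". Section 2.7 lists age and education among the items that CAIDE scores. Section 5.1.1 makes the association between CAIDE and poorer s-MoCA a study objective, framed around modifiable factors.

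Section 4 plans multivariate regression without naming covariates. It offers statistical adjustment and sensitivity analyses as measures against selection bias.

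**The concern.** The introduction (section 1.1) describes MCI as "a transitional phase between cognitive ability decline due to age and the terminal stage of CI, dementia". It therefore recognises a decline due to age that is not yet impairment. A single raw threshold over an open-ended age range cannot separate the two. Schooling raises the same question, because serial sevens, one-minute fluency, abstraction and clock drawing may depend on education, although the documents do not say so.

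If intact scores do fall with age or less schooling, three results are affected. The CI+ share depends partly on who visits the pharmacy. The physician-confirmed share varies between strata because false labels do. The CAIDE contrast compares a group selected partly on age and schooling with its complement, using a score that counts age and schooling. A positive CAIDE result could then arise with no contribution from blood pressure, cholesterol, BMI or physical activity. Adjusting a later comparison does not change the label, so it cannot correct the first two results.

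**Working it through.** **The plan's own figure.** Section 2.2 gives a minimum of 385 for 95% confidence, a 5% margin and a population of 2,033,555. With p = 0.5 (assumed, not stated), n0 = 1.96² × 0.25 / 0.05² = 384.15. The finite-population correction gives 384.07, rounded up to 385. The figure reproduces and is not affected by this point.

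**False labels in one stratum.** The documents give no s-MoCA mean, SD, sensitivity or specificity, so what follows is illustration. For intact people, the share at or below 12 is Φ((12.5 − (mean − drop)) / SD), where the drop is the assumed loss from higher age or less schooling.

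| Mean, SD (assumed) | No drop | 0.5 | 1.0 | 1.5 | 2.0 |
|---|---|---|---|---|---|
| 14.0, 1.5 | 15.9% | 25.2% | 36.9% | 50.0% | 63.1% |
| 14.5, 1.5 | 9.1% | 15.9% | 25.2% | 36.9% | 50.0% |
| 14.0, 2.0 | 22.7% | 30.9% | 40.1% | 50.0% | 59.9% |
| 14.5, 2.0 | 15.9% | 22.7% | 30.9% | 40.1% | 50.0% |
| 14.0, 2.5 | 27.4% | 34.5% | 42.1% | 50.0% | 57.9% |
| 14.5, 2.5 | 21.2% | 27.4% | 34.5% | 42.1% | 50.0% |

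A 1-point drop moves the range from 9–27% to 25–42%. With no drop there is no excess.

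**Effect of the mix on the two shares.** Take a younger and an older stratum, sensitivity 0.8, every CI+ person followed up and the physician always correct (all assumed). CI+ share = Σ weight × [prevalence × 0.8 + (1 − prevalence) × false-positive rate]. Confirmed share = true positives / CI+. The older stratum's weight moves from 30% to 70%.

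| Case | False positives, younger/older | True CI, younger/older | CI+ share | Confirmed share |
|---|---|---|---|---|
| A | 20% / 20% | 10% / 10% | 26.0% to 26.0% | 30.8% to 30.8% |
| B | 20% / 20% | 10% / 25% | 28.7% to 32.3% | 40.4% to 50.8% |
| C | 20% / 30% | 10% / 10% | 28.7% to 32.3% | 27.9% to 24.8% |
| D | 20% / 50% | 10% / 10% | 34.1% to 44.9% | 23.5% to 17.8% |
| E | 20% / 50% | 10% / 25% | 35.4% to 48.0% | 32.7% to 34.1% |

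B and C give the same CI+ shares, although in B the trend is real disease and in C it is false labels. The older stratum's CI+ rate is 0.25 × 0.8 + 0.75 × 0.2 = 0.35 in B and 0.1 × 0.8 + 0.9 × 0.3 = 0.35 in C. The confirmed share within that stratum separates them: 0.20 / 0.35 = 57% against 0.08 / 0.35 = 23%.

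**Effect on the CAIDE contrast.** Take case D with equal stratum weights, and controls taken as those above 12 (assumed). CI+ rates are 0.1 × 0.8 + 0.9 × 0.5 = 0.53 in the older stratum and 0.1 × 0.8 + 0.9 × 0.2 = 0.26 in the younger. The older share is 0.265 / 0.395 = 67% of CI+ and 0.235 / 0.605 = 39% of controls, although true CI is equal in the two strata. Any CAIDE points for age would therefore differ between the groups with the modifiable components equal. In case B the older share is 0.175 / 0.305 = 57% against 0.325 / 0.695 = 47%, this time through real disease. In neither case does total CAIDE isolate the modifiable part.

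**The case against.** The article treats ≤12 as a screen. Section 1.1 says a poor result does not establish CI, section 2.9 has patients told that it is not a diagnosis, and section 3 speaks only of suspicion and has a physician confirm. False positives are expected. The source cited for the cut-off is not at hand and may have addressed age and education. Covariates and strata are commonly left to an analysis plan, and section 4 does mention adjustment.

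Much of this stands. The premise that intact scores fall with age or less schooling is not in the documents, and every input to the illustration except the cut-off is assumed. The normal curve is also rough on a scale that stops at 16: with mean 14.5 and SD 2.0 it puts 16% of people above 16.5.

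A reader might infer that the CI+ and confirmed shares mainly track age and education. The documents do not support that. True CI may itself rise with age, and the confirmed share rises in case B, falls in D and stays almost flat in E. A reader might also set the rise in false labels against the 5% margin in section 2.2. Those are unlike quantities: one is a rise among intact people in one stratum, the other the precision of an overall proportion.

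What the objection does not remove is that the label and the comparisons built on it are fixed in the article. Physician confirmation sorts the labels only among those already CI+, and it does nothing for the CAIDE and ACB contrasts, which use the screening label. The stated adjustment is aimed at selection bias.

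**Conclusion.** The point holds in conditional form. One raw cut-off sets CI+ for everyone, and age and school years are recorded but not used in any stated check of it. If intact scores fall with either, false labels differ by stratum, both shares may partly reflect the mix, and the CAIDE contrast is partly built in. The size is unknown: zero with no drop, and 25–42% false labels instead of 9–27% in the affected stratum for a 1-point drop under the assumed means and SDs.

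The overlap with CAIDE is the most consequential part. It decides whether an association can be read as concerning modifiable factors or only age and schooling. This warrants a change to the analysis. It does not show that the cut-off is wrong.

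**What to change.** Leave ≤12 as the screening and referral rule, and add to sections 3 and 4:

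- **Shares by stratum.** Report the CI+ share and the physician-confirmed share by age band and by school years.
- **ACB.** Adjust the CI+ versus control comparison for age and school years. Repeat it with continuous s-MoCA as the outcome and the same covariates.
- **CAIDE.** Add an analysis of its components other than age and education, adjusted for age and school years. Base any claim about modifiable factors on that analysis and not on total CAIDE. Sex remains among the components but is not modifiable.

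Redefining CI+ on an age- and education-residualised score with the same number of cases is not advised. It fixes the CI+ share by construction, people newly labelled would have no planned confirmation data, and it removes part of what CAIDE measures. For the same last reason, total CAIDE should not be required to hold under such a definition.

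The cost is protocol wording and a few extra analyses, with no new data collection. The CAIDE association may look weaker.

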### Strengths and limitations of this study

5.2

The study focuses on at-risk patients with CIs within pharmaceutical care in a community pharmacy. Implementing cognitive screening in the pharmacy setting may contribute to the early identification of patients with CI, reducing the pressure on ambulatory care associated with CI prevention.Data will be collected using easy-to-use cognitive screening by a pharmacist.The realization of cognitive screening, correct evaluation of results and interpretation, and the pharmacist’s final decision about referring a patient to a physician will depend on their experiences and critical judgment. Hence, the education of pharmacists in their training program is a crucial stage of this study. It is also important to consider the patient’s other comorbidities, for instance, whether there exists a bidirectional relationship between depressive disorder and cognitive deficits, which may affect the outcome of screening tests. The exclusion of institutionalized older adults may limit the generability of the study cohort.Pharmacists must be able to communicate outcomes concerning patients’ conditions. Collaboration between pharmacists and physicians is important because a patient with suspected CI identified by a pharmacist cannot be diagnosed with CI without the doctor’s confirmation.Furthermore, various tools can characterize the anticholinergic burden score differently. While one tool can classify drugs such as clopidogrel, furosemide, and zolpidem as potentially anticholinergic, according to another tool (e.g., the ACB Calculator), they have no increased risk.

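### Outcomes section refers every patient with s-MoCA ≤12, but the Physician referral section refers low scorers by listed group and pharmacist judgment, so physician confirmation may cover only a selected subset of CI+

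*Protocol article*

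**What the plan says.** Section 3 (Outcomes) sets the cut-off at 12 points or fewer on the s-MoCA and calls these patients CI+: "These patients will be defined as those with suspected CI (CI+) who will be referred for medical examination". No second condition is attached. The next sentence commits the study to recording whether a physician confirmed the suspicion.

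Section 2.10 (Physician referral) describes what happens in the pharmacy. It opens with a judgment made for each patient: "the pharmacist will specifically consider whether their condition requires a visit to the doctor or a pharmacy consultation is sufficient". It continues: "Specific groups of patients are referred to a physician if they score decreased cognitive abilities on the s-MoCA test". Six groups follow, in paraphrase:

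- memory complaints
- an early warning sign of dementia
- raised risk on CAIDE
- no routine preventive check-ups
- prolonged use of at-risk drugs
- prolonged use of over-the-counter memory products

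The same section has one rule that covers everyone, for a different purpose: "Every patient in the study should be referred to a general practitioner for a preventive check-up if they have not had one" within the last two years. It is not tied to the s-MoCA score.

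Section 5.2 (Strengths and limitations) notes that "a patient with suspected CI identified by a pharmacist cannot be diagnosed with CI without" a doctor's confirmation.

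**The concern.** The two sections give different conditions for the same act. In section 3 a low score is sufficient for referral. In section 2.10 the text asks for a low score together with membership of a listed group, and gives the pharmacist a further choice that is not closed off for patients at or below the cut-off.

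Two things are at stake. First, a CI+ patient who is not referred may never have a physician's verdict. Two of the six groups are defined by CAIDE risk and at-risk medication, which the study also compares between CI+ and controls. A confirmation result obtained under section 2.10 could therefore describe a subset of CI+ selected partly on the factors under study, which is partial verification. Second, two pharmacies reading different sections could handle the same score differently, and a patient with a positive screen could leave without a physician visit.

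Referral happens in the pharmacy. An analysis plan can choose a denominator, but it cannot supply a verdict for a patient who was never examined.

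**Working it through.** **The texts side by side**

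| Place | Who is referred | Force |
|---|---|---|
| Section 3 | All with s-MoCA ≤12 | Unconditional |
| Section 2.10, group sentence | Low scorers in one of six groups | Conditional on group |
| Section 2.10, opening sentence | Any patient the pharmacist judges to need a visit | Discretionary, no exemption for CI+ |
| Section 2.10, check-up sentence | Anyone without a check-up in two years | Unrelated to score |

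Take a patient who scores 11 and belongs to none of the six groups. Section 3 refers this patient. The group sentence in section 2.10 does not, and the opening sentence permits a consultation only. The check-up sentence does not help: belonging to none of the groups means that check-ups are regular. Section 2.9 (Patient counseling) mentions giving results "following initial screening or, if necessary, after retesting 6 months later", but the visible text does not connect the retest to referral, so it does not settle the matter either.

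**The plan's own number, used below as the base**

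Section 2.2 gives a minimum of 385 for 95% confidence and a 5% margin. With an expected proportion of 0.5 (assumed; the article does not state it):

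n0 = 1.96² × 0.5 × 0.5 / 0.05² = 384.15

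The finite population correction for N = 2,033,555 gives 384.07. Both round up to 385, so the figure reproduces. It is not affected by this point.

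**Illustration of size (every input except 385 is assumed)**

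- Share of participants who are CI+: 20% to 40%, so 385 × 0.20 = 77 to 385 × 0.40 = 154 patients.
- a = share of CI+ who fall in a listed group.
- p1 and p0 = confirmation rates inside and outside the groups, with p1 − p0 from 0 to 30 percentage points.

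Unreferred under the group sentence = n(1 − a).

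The confirmed share among referred patients is p1. In all CI+ it is a·p1 + (1 − a)·p0. The difference is (1 − a)(p1 − p0).

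| a | Unreferred, n = 77 to 154 | Difference if p1 − p0 = 10 / 20 / 30 points |
|---|---|---|
| 1.00 | 0 | 0 / 0 / 0 |
| 0.90 | 7.7 to 15.4 | 1.0 / 2.0 / 3.0 |
| 0.80 | 15.4 to 30.8 | 2.0 / 4.0 / 6.0 |

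If p1 = p0 the difference is 0 for any a. So with a between 0.80 and 1.00, between 0 and about 31 patients go unreferred, and the confirmed share shifts by 0 to 6 points. A lower a would enlarge both: at a = 0.60 the unreferred number is 0.4 × 77 = 31 to 0.4 × 154 = 62. Individual pharmacist discretion could add an amount that the article gives no means to estimate.

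**The case against.** The best reply is that the sections can be reconciled. Section 2.10 does not say that only the six groups are referred, and it speaks of decreased abilities without restating the cut-off. Section 3 is the one place that defines CI+ and ties that definition to referral. The list could be a set of priority cases. This reading is possible, but the text does not state it, and the opening sentence of section 2.10 would still allow a consultation alone for a CI+ patient.

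Figures 2 to 4 and the supplementary tables are not visible, and section 2.10 points to Figure 4. They may show the intended rule. That limits how firmly one can say what pharmacies would do, but the two sentences would still need to agree.

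A reader might also count section 2.9 ("patients may be referred to a physician if their condition requires it") and section 5.2 ("final decision about referring a patient to a physician will depend on their experiences and critical judgment") as further contradictions. They do not carry that weight. The first covers all screened patients, including those above the cut-off, where discretion is expected. The second is a limitations statement, and it names pharmacist training as the response.

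The remaining points stand. Physician confirmation is something the study records; it is not one of the three listed objectives, and section 4 names no analysis of it. The groups are broad and overlap the recommended target group in section 2.5.1. The follow-up contact in section 2.10 is not restricted to referred patients, so some unreferred patients may still report a verdict.

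**Conclusion.** The inconsistency is real and should be corrected. Section 3 promises referral of every CI+ patient and a record of confirmation; section 2.10 would allow some of them not to be referred. Nothing in the visible text reconciles the two.

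The size is unknown. The illustrated 0 to 31 patients and 0 to 6 points rest on assumed values for the CI+ share, group coverage and confirmation rates, and the true effect may be zero. Confidence is medium, because the figures are unseen.

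Two stronger inferences are not supported. One is that the study's main comparisons are biased: CI+ status comes from the s-MoCA score alone, so the CAIDE and ACB comparisons with controls do not depend on who is referred. The other is that low scorers outside the six groups will certainly be missed: section 2.10 does not exclude them in so many words.

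**What to change.** Amend section 2.10, and Figure 4 if it differs, to say that every patient with s-MoCA ≤12 is referred to a physician, as section 3 already states. Present the six groups, if they are kept, at most as priority flags among low scorers. Limit the pharmacist's choice between consultation and referral to patients above the cut-off. Do not turn the six groups into a new referral rule for patients above 12; no section supports one. If the six-month retest is meant to precede referral for some low scorers, say so in both sections.

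Report confirmation with all CI+ patients as the denominator, and count those without feedback as unknown, not as unconfirmed.

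The cost is one or two sentences and possibly a figure edit. The downside is somewhat more physician referrals, to which section 3 already commits the study.
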